### Hypotheses

#### Primary hypotheses

At post-treatment, participants in the intervention group, compared to control group, will show improvement in sleep health (physiological and self-reported) and in indices of stress and psychopathology (biological and self-reported), including perinatal depression (PND) and anxiety. Improvement in biological and self-reported indices of psychopathology and stress will be mediated by improvement in insomnia symptoms and sleep dimensions.

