### Sample size

To estimate required sample size for adequate power of the clinical trial, we used as primary outcome peripartum depression (PDS) at post-treatment. A study that compared scores on the Edinburgh Postnatal Depression Scale (EPDS) in 132 women divided into two groups, cognitive-behavioral therapy for insomnia (*N* = 89) or control group (*N* = 43), before, during and after pregnancy [35] was used. The software G-Power was used to estimate sample size: 114 women in total would be needed to have an effect power of at least 80%. Drop-out rates in previous studies were around 5 to 16% for post-treatment and short follow-ups [28, 33] and around 17% for 6 months follow-up [36]. We plan to recruit 150 participants, accounting for a dropout rate of 24%.

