### Outcomes

#### Primary outcomes

Stress reactivity: salivary cortisol level assessed by saliva sample provided by participants through swabs twice a day once at baseline, follow-up 1 and 5.Sleep efficiency: Total Sleep Time (min)/Time In Bed (min) expressed in percentage and assessed trough actigraphy monitoring. Assessed one week at baseline, follow-up 1, follow-up 5.Depressive symptoms: Edinburgh Postnatal Depression Scale (EPDS) [43] total score. EDPS scores > 10 will be considered as indicative of PND. Assessed at baseline, follow-up 1 and 5.Mothers’ Insomnia symptoms: Insomnia Severity Index (ISI) [39] total score. Assessed at baseline, follow-up 1–5.Anxiety symptoms: Generalized Anxiety Disorder questionnaire (GAD-7) [44] total score. Assessed at baseline, follow-up 1–5.Valence of affective states at morning and evening: visual scale in sleep and emotional diaries. Assessed one week at baseline, follow-up 1, follow-up 5.Arousal of affective states at morning and evening: visual scale in sleep and emotional diaries. Assessed one week at baseline, follow-up 1, follow-up 5.Emotion regulation strategies: Cognitive Emotion Regulation Questionnaire – Italian Short-Version (CERQ-IS) [45] subscales scores. Assessed one week at baseline, follow-up 1, follow-up 5.

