### Statistical analysis

Analyses will be performed by a professional biostatistician ([name]). For all outcomes, intent-to-treat analyses (ITT) will be performed including all randomized women in the statistical analyses. Descriptive statics will be reported, including recruitment rate, dropout rate, and data completion rate. A detailed flow chart of study participants will be provided. Only data from those completing the trail will be analysed. Baseline characteristics of non-completers and completers will be compared. Independent t-test and Chi-square test will be conducted to compare randomized groups on baseline characteristics. Significant differences between dropouts and retained participants will be investigated with comparisons on baseline and outcome characteristics. Multivariate linear regressions will be used for testing associations with insomnia during pregnancy and postpartum depression. A multivariate mixed effects model analysis will be performed to test the interventions efficacy over time. Within- and between-groups differences will be measured including as factors the Group (A, B1, B2) and TIME (Pre-; Post-; last weeks of pregnancy; Birth; 3; 6) and as outcome all endpoints which will be collected at all assessments. For all analyses statistical significance is set at p-values < 0.05.

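### The protocol names one primary outcome when sizing the trial and eight unranked ones in the outcomes list, applies 0.05 to every analysis, and does not say which result confirms the primary hypothesis

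*Protocol article*

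**What the plan says.** Four places in the protocol article bear on this point.

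- **Sample size.** The calculation has one primary outcome: "we used as primary outcome peripartum depression (PDS) at post-treatment". The scale is the EPDS. The stated result is 114 women for at least 80% power, raised to 150 for 24% dropout.
- **Outcomes.** Under the heading "Primary outcomes" stand eight entries in no declared order: salivary cortisol, actigraphic sleep efficiency, EPDS, ISI, GAD-7, affect valence, affect arousal and CERQ-IS. Some have parts. Cortisol is collected "through swabs twice a day once at baseline, follow-up 1 and 5", the diary items are "Valence of affective states at morning and evening" and "Arousal of affective states at morning and evening", and CERQ-IS is scored by subscale.
- **Primary hypotheses.** At post-treatment the intervention group, compared with control, "will show improvement in sleep health (physiological and self-reported) and in indices of stress and psychopathology (biological and self-reported"), with perinatal depression and anxiety included. Maintenance at later follow-ups is the secondary hypothesis.
- **Statistical analysis.** A mixed model with group and time as factors is planned, and "For all analyses statistical significance is set at p-values < 0.05".

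**The concern.** The Sample size and Outcomes sections cannot both define the confirmatory endpoint. EPDS is the primary outcome in one and an unranked one of eight in the other. With 0.05 applied throughout and no success rule, a reader of the results could not tell whether the trial met its aim if, say, evening arousal were significant and EPDS were not.

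A decision depends on this. The Dissemination plan says that medical services will be approached about implementation if the trial substantiates efficacy, but what counts as substantiation is not defined. If one significant result out of eight were enough, the claim would not carry a 5% error rate. If all eight were needed, the power statement would not apply to it.

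**Working it through.** **The plan's own figure.** 114 / (1 − 0.24) = 150, so the recruitment target follows from 114. The 114 itself cannot be rebuilt, because the article gives no effect size, standard deviation, test or sidedness. It concerns EPDS only.

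**Inputs.** Eight primary outcomes (Outcomes section) and 0.05 per analysis (Statistical analysis section). Assumed, because not stated: two-sided tests, one test per outcome, and a common pairwise correlation r between test statistics, varied from 0 to 0.9.

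**Reading 1: any one significant primary outcome supports a claim.** With no true effect and k independent tests, P(at least one p < 0.05) = 1 − 0.95^k.

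- Eight outcomes: 1 − 0.95^8 = 0.337.
- Cortisol, valence and arousal each split in two, the other four single-score outcomes, and CERQ-IS as one score: 2 + 2 + 2 + 4 + 1 = 11 tests, and 1 − 0.95^11 = 0.431.

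For correlated tests, equicorrelated normal simulation (1,000,000 draws per setting) gives:

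| r | 8 tests | 11 tests |
|---|---|---|
| 0 | 34% | 43% |
| 0.3 | 30% | 38% |
| 0.5 | 25% | 30% |
| 0.7 | 19% | 22% |
| 0.9 | 12% | 13% |

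The number of CERQ-IS subscales is not given; each one tested separately adds to the 11. Repeated time points and contrasts with Group A are not counted.

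**Reading 2: all eight must be significant.** The false-positive rate does not inflate, but joint power cannot exceed the power for EPDS alone. If each outcome had 80% power and the tests were independent, joint power would be 0.8^8 = 0.168, about 17%. Positive correlation raises it. It would equal the EPDS power only if the other seven were significant whenever EPDS was.

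**Cost of keeping eight primaries with an adjustment.** Bonferroni gives 0.05 / 8 = 0.00625 per test. With 38 per arm (noncentral t, two-sided), the standardized difference detectable with 80% power rises from 0.65 to 0.84, and power at 0.65 falls from 80% to about 51%.

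**The case against.** The strongest reply is that the plan nowhere says one significant result is enough. The primary hypothesis is worded as a conjunction: sleep health and also stress and psychopathology. The discussion repeats that form. A reader might infer that any single p < 0.05 confirms the hypothesis as written. The text does not support that; it is one possible reading, and the percentages under Reading 1 depend on it. But the text does not state an all-must-succeed rule either, and that reading leaves the power unsupported.

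A second reply is that the model is called multivariate and is restricted to endpoints gathered at every assessment. Among the primary outcomes, the Outcomes section lists only ISI and GAD-7 at baseline and all five follow-ups. Taken strictly, two tests give 1 − 0.95^2 = 9.75% if independent. However, that reading leaves EPDS, the sized outcome, outside the efficacy model. The same section also promises intention-to-treat analyses for all outcomes, and no joint test is described.

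A third reply is that an article may leave the multiplicity procedure to an analysis plan that is not shown, and that a 0.05 threshold does not exclude adjusted p-values. This stands: the absence of a named procedure is not the point here. An unseen plan would not, however, remove the conflict between the Sample size and Outcomes sections.

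**Conclusion.** The protocol contradicts itself on what is primary and gives no rule for success. This needs to be fixed before outcome data are seen.

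The size is conditional. If any one primary outcome may carry the claim, the family-wise error over eight tests is about 12–34%, depending on an undocumented correlation, and somewhat more if time-of-day readings and subscales are tested separately. If all eight must succeed, the error rate is not inflated, but the stated 80% power is not established for that claim.

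Three stronger statements go beyond the documents:

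- 25% is not a lower limit. It corresponds to r = 0.5, and higher correlation brings the figure down.
- Rates such as 43% for 11 tests or 62% for 19 (1 − 0.95^19, if nine CERQ-IS subscales are assumed) treat readings and subscales of the same instrument as independent, which is hardest to defend there. The article also does not say that the two cortisol samples are tested separately.
- It would be wrong to say that EPDS has no special standing. The Sample size section gives it that standing, and the Outcomes section fails to carry it over.

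**What to change.** Reconcile the Sample size and Outcomes sections before outcome data are seen:

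1. Name EPDS total at follow-up 1, B2 versus B1, as the single primary endpoint, tested at two-sided 5%. This follows the choice already made for sizing. State that the efficacy model includes EPDS although it is not listed at all six assessments.
2. Make the other seven outcomes secondary. Test them by Holm or in a fixed order only if EPDS is significant, counting every time-of-day and subscale test in the family. Alternatively, report them as exploratory without confirmatory claims.
3. Treat follow-up 5 as secondary, in line with the stated secondary hypothesis.
4. Make the change through the amendment route under Ethical aspects, which already provides for updating the registered protocol.

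Declared co-primaries or an adjusted family of eight would also remove the contradiction, but at the loss of power shown above. The recommended change costs wording and an amendment, with no extra participants on account of multiplicity. Its downside is that seven outcomes lose primary status and face stricter thresholds.

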### Dissemination plan

All study findings will be disseminated in anonymous and aggregated forms. Key findings of the study will be disseminated to academic (presentation at conferences, publication in high impact journals) and non-academic (websites of psychological and medical associations, social media) audiences. If the trial substantiates the efficacy of the psychoeducation intervention, medical services for pregnancy and peripartum care will be contacted to explore opportunities to implement and disseminate the intervention to pregnant women suffering from insomnia symptoms.

### Expected results and discussion

Women are at higher risk than men to develop psychopathological problems, including chronic sleep difficulties [2]. This gap is particularly relevant during specific women’s life period, i.e. puberty, peripartum, and menopause [56]. The peripartum represent a stressful period marked by societal, physiological, and hormonal changes, the adaptation to which can have long lasting consequences on the women, the newborn, and the whole family system [25]. The need to promote maternal mental health has been included in the World Health Organization’s agenda, and several papers have stressed the importance of sleep health for peripartum wellbeing [14, 15, 57]. Recently, there is a grows of clinical trials based on CBT-I for pregnant women with promising results [25]. Here we propose MOTHERS as a new preventive approach to promote sleep health in pregnant women, and to prevent the biopsychological cascade of events that can lead to negative pregnancy outcomes, post-partum maternal psychopathology, and children’s sleep impairments.

Three groups of women will be compared longitudinally: one group (B2) with sleep difficulties randomized to the psychoeducational intervention, one active control group (B1) with sleep difficulties randomized to an educational placebo intervention, and a group (A) without sleep difficulties serving as a passive control group. We expect that women in the intervention group will show, compared to the placebo group, post-intervention significant improvement in physiological (actigraphy) and self-report (questionnaire, sleep diaries) indices of sleep health as well as of stress reactivity (salivary cortisol levels) and psychopathology (self-report). MOTHERS includes modules directed to promote evidence-based self-management of sleep health, delivering basic knowledge about sleep during pregnancy, factors inhibiting or promoting sleep heath, and management of sleep in the postpartum as a family issue. The importance of sleep health as a positive and multidimensional concept is a key content delivered in the intervention, as each dimension of sleep health can have negative consequences on overall health [58]. While research has primarily focused on the effect of sleep duration on pregnancy outcomes [59], other dimensions are also important. For instance, sleep timing is commonly changed during pregnancy, but the effects of this changes are rarely considered. Fatigue is common during pregnancy, however sleepiness and fatigue are different constructs, and it is important to recognize this difference, as going to bed when still alert weaken the bed-sleep association. With knowledge of sleep health dimensions as a continuum, the person can be instructed to identify specific areas of vulnerability (e.g., late sleep timing) and strengths.

Programs aimed at improving sleep health are often focused on sleep hygiene [60, 61]. Sleep Hygiene Education (SHE) aims at providing information about factors interfering with sleep, including lifestyle factors (e.g., diet and substance use) and environmental factors (e.g., noise, temperature). While SHE is included in standard CBT-I protocols, it is not recommended as a standalone intervention for clinical sleep difficulties [26]. The use of SHE to promote sleep health in the general population is also met with some challenges and limitations. While some recommendations, such as care of the sleep environment and regular bedtime, are important to deliver in preventive programs, they may not be enough for people with already basic knowledge of sleep-interfering factors [26]. Moreover, SHE programs seldom include self-monitoring of sleep (e.g., through diaries), which is an important component of sleep improvement [62]. SHE also does not include a focus on perpetuating factors of insomnia disorders, i.e. cognitive, emotional, and behavioural factors, which can influence sleep-wake regulation [63–69].

MOTHERS delivers basic information on sleep regulation and psychological (cognitive, emotional, and behavioural) factors influencing sleep. The intervention provides evidence-based recommendation to manage sleep-interfering factors, including CBT-I derived strategies. MOTHERS also covers transversal competence, such as emotion regulation and management of everyday worries, to modulate cognitive and emotional factors which are associated with chronic insomnia disorder [70, 71] and a range of psychopathological conditions [72, 73]. The RCT protocol includes the use of sleep diaries during the 6 weeks of intervention, providing women the opportunity to self-monitor sleep-wake activities.

We expect that improvement in sleep health would lead to improvement in biological and self-report indices of wellbeing in the post-partum. Indeed, sleep difficulties in the peripartum increase the risk of perinatal depression (PND) and anxiety [15]. Moreover, sleep difficulties represent stressful experiences, which can alter the regulation of the stress response during pregnancy [21]. These alterations, in turn, can trigger epigenetic mechanisms and thus influence the stress regulatory systems of newborn with potential long-lasting effect on sleep regulation and psychopathology [21]. This first study will focus on women who reports no use of alcohol and smoking during pregnancy and no somatic or mental comorbidities, as these factors may influence and alter sleep. It should be noted that these same factors are associated with increased risk of PND [74]. If the present trial will have the expected results, MOTHERS could be tested in women with insomnia presenting risk factors for PND and thus more vulnerable to post-partum psychopathology.

Digital interventions are particularly suitable to pregnant women, as they break down barriers to psychological interventions, such as managing other prenatal health appointments and preserving personal time off for maternity leave [33]. There is thus a need for evidence-based psychoeducational programs which can be delivered digitally or in-person in the context of routine care of pregnant women. Sleep health is an important component, as it is routinely done with nutrition and physical activity. MOTHERS is intended to be delivered digitally but it is also adaptable as an in-person program. Moreover, women in the intervention conditions will also have the weekly opportunity, during the interventions, to have direct contact with an expert CBT-I clinician ([name]) to express difficulties with the intervention’s contents and to have personalized feedback about their specific symptomatology. This is expected to have positive effects on women with specific difficulties and to increase adherence to the intervention, as adherence to guided digital CBT (dCBT) is higher than to unguided programs [75]. Moreover, when possible guided dCBT-I is preferable, as evidence suggest its superior efficacy to unguided dCBT-I [76, 77].

In conclusions, MOTHERS has several strengths and implications for familiar wellbeing in the peripartum. The intervention is innovative as it focuses not on a restricted series of sleep hygiene rules, which may be not appropriate for some individuals, but on overall promotion of sleep health, delivering knowledge and promoting attitude to self-manage sleep health. It is founded on the concept of sleep health as a positive construct [58] and on the 5 principles of good sleep health, which are universally adoptable and thus suited for different conditions [78]. It also includes basic information derived from models of insomnia disorder about behavioural, emotional, and cognitive processes influencing sleep health, and adapted CBT-I techniques to modify sleep-disrupting processes. The study includes assessments at the biological (salivary sample), physiological (actigraphy), and self-report data to broader the understanding of the multiple complex impact of sleep health and its promotion during pregnancy. We also included a pre- and post-intervention assessment and 4 follow-ups to tackle short- and long-term effects of the MOTHERS programs and the longitudinal psychobiological changes in sleep and wellbeing across pregnancy. The inclusion of assessment of partners’ and children’s sleep and wellbeing aims to further deepen the understating of sleep and psychopathology in the family context. Furthermore, intergenerational effects of maternal sleep and stress on children’s sleep problems and overall health will be assessed though questionnaire and diaries, and a new biomarker of maternal poor sleep as a stressing condition will be tested (the DNA methylation of the FKBP5, BNDF, and NR3C1 genes).

## Data Availability

No datasets were generated or analysed during the current study.
